### Surgeon risk adjustment

4.2

Given that the surgical difficulty and peri- and postoperative complication risks estimated by the calculator may not encompass every potential comorbidity, an ad hoc provision will be introduced, allowing surgeons to adjust the estimated risks reasonably. Recognising the inherent uncertainty (confidence interval) around the calculated risks, clinicians will be permitted to modify the risk and difficulty estimates within the confidence interval for each outcome measure. Surgeons will be allowed to increase the estimated risks by up to 30 points (on a scale of 0–100) if deemed necessary.

To evaluate the relative value of generic versus surgery-specific risk models, surgery-specific models will be developed for the three most common surgical specialities in the database (RC, RP, and PN). The C-indices, HL analyses, and Brier scores for the generic model will then be compared against those of the surgery-specific models applied to the same patient subgroups defined by subspeciality.

By creating a single model applicable across a wide range of surgical outcomes and difficulties, the aim is to streamline the preoperative risk assessment process. However, it is acknowledged that, in certain circumstances, surgery-specific models may yield more precise risk estimates. This suggests that the optimal strategy may involve a balanced approach, incorporating the simplicity of a generic model while maintaining the accuracy of speciality-specific models where appropriate.

### Internal validation

4.3

Internal validation of the prediction models will be conducted by randomly splitting the analytic dataset into two subsets: a developmental dataset (two-thirds of the total data) and a validation dataset (one-third of the total data). The C-indices, HL analyses, and Brier scores from the logistic regression analyses will be compared between the developmental model applied to the developmental dataset and the same model applied to the validation dataset.

The use of stepwise, forward-selection logistic regression has faced criticism, particularly in small samples, regarding variable selection and the accuracy of the coefficients and standard errors. However, such criticisms are less relevant when applied to the large sample sizes present in this study. To further test the robustness of the model, bootstrap resampling will be employed for the postoperative mortality model. Full-variable logistic regression models will be performed on each bootstrap sample. The variables will then be ranked by the magnitude of the Wald χ^2^ statistic, and the average rankings from the bootstrap samples will be compared with the order of entry of variables during the forward selection stepwise regression analysis. As such, all steps described above aim to minimise overfitting and improve predictive accuracy.

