2	To predict intra-, peri-, and postoperative outcomes by considering preoperative factors only, to optimise the allocation of critical care resources or defining teaching-appropriate cases before surgery starts
3	To determine surgical difficulty as a separate matter to judge surgical performance by improving the comparison of intra- and postoperative outcomes between surgeons and between different interventions
4	To define parameters that make certain operations (and approaches) for anaesthetists and urologists more difficult
5	To create several indices (surgical risk and difficulty estimation) that are calculated before and immediately after surgery

The surgical difficulty and risk estimation tool will integrate five categories of patient-specific parameters (Table 2):1.Preoperative (known, expected) patient-specific characteristics and conditions (eg, body mass index [BMI], ASA score, sex, prior abdominal surgery, and comorbidities)2.Intraoperative (unknown or unexpected) body/patient-specific characteristics and conditions (eg, bleeding tendency, restricted operative space due to a narrow bony pelvis, or extensive adhesions)3.Preoperative targeted organ-specific parameters (eg, tumour size and location, organ anatomy and morphology, or a history of prior interventions on the targeted organ such as biopsies or transurethral resection of the prostate preceding prostatectomy)4.Intraoperative targeted organ-specific parameters (eg, fibrosed periprostatic tissue or tumour extension beyond the targeted organ).5.Unexpected/unknown postoperative conditions prior to discharge or within 24 h (eg, acute kidney injury, quantified by a decrease in glomerular filtration rate [ml/min])

Surgical and anaesthetic parameters will be evaluated independently to account for the influence of case volume and individual learning curves on surgical complexity and risk. The key variables will include the total case volume, frequency of procedures performed within a defined period, and complexity of prior cases. Additionally, institutional case load will be considered when estimating perioperative morbidity risk (eg, in tertiary referral centres).

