### Identification and description of factors

3.3

In the initial phase of the study, risk-predicting parameters will be defined using data from the CAMUS Collaboration cystectomy database, which will include pre- and intraoperative variables sourced from 178 centres worldwide. Additional parameters from a prospective open cystectomy database maintained by the Urology Department at the University of Bern will further enhance data collection. The difficulty estimation score will be developed and validated using these data, supplemented by prospectively collected parameters detailed in round 1 of the study.

The RC cohort will be selected as the primary focus due to its high complication rate and clinical relevance. In subsequent phases, the scoring system’s performance will be assessed in various patient cohorts who have undergone RP, PN, radical nephrectomy (RN), radical nephroureterectomy (RNU), and retroperitoneal lymph node dissection (RPLND).

The first Delphi round will involve expert consensus to identify parameters influencing peri- and postoperative morbidity, mortality, and surgical difficulty. For example, parameters relevant to RP will be outlined in Supplementary Tables 1 and 2. Experts will be guided by the results derived from nomograms. Organ-specific factors, as part of the organ-specific scoring system, will also be examined for procedures such as RC, RP, PN, RN, RNU, and RPLND, with further details provided in Supplementary Table 3.

To assess the impact of these parameters on both difficulty and risk, a comprehensive description of the associated conditions and characteristics will be required. These parameters will be categorised according to a five-level scale of difficulty: easiest, intermediate easy, standard, intermediate difficult, and most difficult. For instance, preoperative BMI ranges will be classified as follows: BMI 18–22 kg/m^2^ will correspond to the easiest grade, while BMI >40 kg/m^2^ will be categorised as most difficult. Similarly, for organ-specific factors such as prostate size in RP, a prostate volume of 20–30 cc on magnetic resonance imaging will represent the easiest level of difficulty, whereas a volume exceeding 200 cc will be classified as most difficult.

Notably, multiple conditions may be associated with the same level of difficulty. For example, multiple prior open procedures or laparoscopic surgeries involving mesh insertion may be considered of intermediate difficulty.

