Logistic regression will be used to examine the relationship between major complications/death, and the risk index score (treated as an ordered categorical variable based on predefined categories) and its components across the three patient cohorts. Model discrimination will be assessed by calculating c-statistics (area under the receiver operating characteristic curve). For model calibration, the Hosmer-Lemeshow (HL) goodness-of-fit test will be used to compare predicted versus observed outcomes between the two cystectomy cohorts. In the final cohort, differences in complication rates across individual scores will be compared using chi-square tests. Additionally, using morbidity (complicated/uncomplicated) and mortality (dead/alive) as dichotomous dependent variables, multiple logistic regression models will be derived. Overall model significance will be assessed via the model chi-square statistic, and differences between observed and expected outcomes will be evaluated using the HL test.

To develop the surgical difficulty index, pre-, intra-, and postoperative parameters and outcome measures will be determined by experienced high-volume surgeons (≥1000 major interventions and >10 yr of surgical experience) using the Delphi method. Pre- and perioperative parameters that potentially increase operative difficulty and risk will be assessed using a 5-point scale, as shown in Supplementary Tables 1–3. Primary outcome measures for surgical difficulty will include operation duration, blood loss and transfusion, use of haemostatic agents, and the surgeon’s judgement (on a scale from 0 to 100).

The performance of the universal surgical risk calculator, which includes multiple specialities and hundreds of procedures, will be compared with the performance of our risk calculators, specifically programmed for this score development. This comparison will be made for individual procedures (eg, RC and RP).

Alternatively, to create risk prediction models, random-intercept, fixed-slope hierarchical models (using SAS GLIMMIX) will be employed. These models account for case clustering within hospitals and impose an empirical Bayes-type shrinkage adjustment. As a result, both universal and procedure-specific surgical risk calculators will be developed. The performance of the universal versus procedure-specific models will be evaluated using three metrics: the c-statistic, the HL statistic (in a revised graphical form), and the Brier score.

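### The random split in section 4.3 does not hold out hospitals, so internal validation cannot show how the models perform across centres or in a new one

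*Protocol article*

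**What the plan says.** Section 4.3 (Internal validation) says: "Internal validation of the prediction models will be conducted by randomly splitting the analytic dataset into two subsets". Two-thirds of the data go to development and one-third to validation. It continues: "The C-indices, HL analyses, and Brier scores from the logistic regression analyses will be compared" between the two parts.

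The data are clustered. The CAMUS cystectomy variables are "sourced from 178 centres worldwide" (section 3.3), and section 3.7 adds a single-centre cystectomy database of 1550 patients.

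Section 4.1 builds the score by logistic regression, taking the points from the regression coefficients. It then offers a second route: "Alternatively, to create risk prediction models, random-intercept, fixed-slope hierarchical models (using SAS GLIMMIX) will be employed". Of these it says: "These models account for case clustering within hospitals and impose an empirical Bayes-type shrinkage adjustment". Section 2.2 adds that "institutional case load will be considered when estimating perioperative morbidity risk".

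Two other internal checks are described. Section 4.1 compares two years of development data with a third year. Section 4.3 bootstraps the mortality model to compare variable rankings. Neither is described as keeping hospitals apart. Section 4.4 leaves generalisability to a later prospective multicentric validation, for which collaborations inside and outside the CAMUS network are still being explored.

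**The concern.** The tool is meant for a web calculator used in many hospitals and for comparisons between hospitals. The property that matters is therefore how well predictions hold from one centre to another. A random split of records places patients of the same hospital on both sides, so whatever is particular to that hospital (case mix, coding habits, baseline complication rate) is shared between development and validation. The validation third is then new patients from known hospitals.

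Two things are at stake. First, the results give no information on the spread of discrimination and calibration across centres, although a database of 178 centres could supply it. Second, a model that carries a hospital-specific term can gain apparent accuracy from that term, which a hospital outside the database would not have.

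**Working it through.** **The plan's own figures.** The article gives no C-index, ICC or hospital sizes. The only related figure is the worst-case sample size of 1180 in section 3.7, which includes 50% for internal validation: 1180 / 1.5 = 786.7. The 50% agrees with a two-thirds/one-third split. The figure says nothing about which hospitals fall where, so it does not bear on this point.

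**Step 1: how many hospitals fall in both parts.** If records are split at random 2/3 to 1/3, a hospital with m patients appears in both parts with probability 1 − (2/3)^m − (1/3)^m.

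- m = 1: 0
- m = 2: 1 − 4/9 − 1/9 = 0.44
- m = 5: 1 − 32/243 − 1/243 = 0.86
- m = 10: 0.98
- m = 20 or more, including the centre with 1550: 1.00 to two decimals

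With 178 hospitals of unequal (lognormal) size, about 78% sit in both parts at a total of 1800 patients, 94 to 95% at 5000, and 98 to 99% at 10000. The totals and the size distribution are assumptions.

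**Step 2: effect on the C-index.** Simulation with 178 hospitals, ten patient-level predictors, about 20% events and 30 replicates per setting. Each model was developed on a random two-thirds of patients, then scored on the remaining third and on 178 new hospitals. All these inputs except the 178 and the split fractions are assumptions.

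*Ordinary logistic model, patient-level predictors only.* The mean gap (random split minus new hospitals) over the 12 settings is 0.001, range −0.008 to +0.014, mostly simulation noise.

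*Ordinary logistic model plus three centre-level predictors with no true effect.* Mean gap 0.004, range −0.005 to +0.017.

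*Random-intercept model scored with the estimated hospital intercepts* (empirical Bayes approximated by a ridge penalty at the true variance), random split v new hospitals:

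| ICC | N = 1800 | N = 5000 | N = 10000 | Gap |
|---|---|---|---|---|
| 0.02 | 0.692 v 0.687 | 0.699 v 0.697 | 0.703 v 0.700 | 0.002 to 0.005 |
| 0.05 | 0.692 v 0.692 | 0.707 v 0.697 | 0.714 v 0.696 | 0.000 to 0.018 |
| 0.10 | 0.713 v 0.680 | 0.720 v 0.689 | 0.727 v 0.691 | 0.031 to 0.036 |
| 0.15 | 0.717 v 0.678 | 0.742 v 0.683 | 0.749 v 0.686 | 0.039 to 0.063 |

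**Step 3: where the gap comes from.** The table changes two things at once: the hospitals and the use of the intercept. Scoring the same random-split validation patients on fixed effects alone separates them. The C-index is then 0.678 to 0.699, against 0.678 to 0.700 in new hospitals, so the gap largely disappears. On those same patients, adding the intercept raises the C-index by 0.002 to 0.004 at ICC 0.02, 0.007 to 0.016 at 0.05, 0.019 to 0.039 at 0.10, and 0.039 to 0.059 at 0.15. The optimism thus comes from scoring with the hospital's own intercept, which a random split permits and a hospital-level split does not.

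**Step 4: a second set of assumptions.** With about 5300 patients, 34% events and five patient-level predictors, the random-intercept model gives 0.703 v 0.698 at ICC 0.03, 0.710 v 0.694 at 0.06, 0.730 v 0.693 at 0.10 and 0.740 v 0.687 at 0.16, that is, gaps of 0.005, 0.016, 0.037 and 0.053. The pattern is the same.

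**The case against.** The strongest reply is that section 4.3 compares results from the logistic regression analyses, whereas hospital intercepts belong to a route that section 4.1 introduces as an alternative. A points score built from regression coefficients has no hospital term and cannot profit from recognising a hospital; one case-load variable could not identify 178 centres either. Even for the alternative models, nothing says that validation patients will be scored with their hospital's intercept, and an article may leave that to the full plan. Finally, the split is labelled internal, and generalisability is assigned to section 4.4; section 5.1.3 says that external validation will be performed.

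Most of this stands, and it limits the claim about size. It does not remove the main point. The alternative models are a stated route to the universal and procedure-specific calculators, and section 4.3 opens with the prediction models in general. The external step has no secured partners, is aimed at high-volume centres and may draw on the same network. Even with no optimism at all, a random split cannot display variation between centres.

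A reader might go further and infer that every hospital sits in both parts and that performance is overstated for any new user. The documents do not support this. The unit of the split is not stated, small hospitals can fall wholly in one part, users in contributing hospitals are not affected, and for the ordinary logistic score the simulated optimism is close to nil.

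A reader might also infer that the calibration check meant to "compare predicted versus observed outcomes between the two cystectomy cohorts" is not independent, since sections 3.2 and 3.3 use both the CAMUS and the single-centre data for development. That may be so if these are the two cohorts meant, but the article does not say. It would also be a matter of pooling, separate from the split.

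**Conclusion.** The point holds as a cheap improvement, not as a demonstrated error. As naturally read, section 4.3 holds out patients and not hospitals, and no other internal check described holds out hospitals. Its results will describe performance in contributing hospitals and will be silent on variation between centres and on a new centre.

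The numerical optimism is conditional. For the ordinary logistic score it is probably negligible, about 0.001 with patient-level predictors and 0.004 with centre-level ones. For the random-intercept models it arises only if they are scored with estimated hospital intercepts: about 0.00 to 0.02 at ICC 0.05 or below, and 0.03 to 0.06 at ICC 0.10 to 0.15. ICC, event rate, total sample size and hospital sizes are assumptions, so the documents do not allow a single figure.

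**What to change.** In section 4.3, replace the random split with internal-external cross-validation:

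- Leave out groups of centres in turn, develop the model on the rest, and validate on those left out. Treat the single-centre cystectomy database as one left-out cohort for models that use parameters shared by both sources.
- Score held-out centres on the fixed effects, without their own hospital intercept, and say so for the hierarchical models.
- Report the spread of the C-index and of calibration across centres alongside the pooled values.

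The data are the same. The cost is a change of wording and some extra computing. Reported performance may be slightly less favourable. The planned external validation remains useful and is not replaced.

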Prediction models for mortality, CCI, blood loss, operating time, and other outcomes will be developed using logistic regression with stepwise selection based on the AIC. Cumulative C-indices will be recorded at each step of model development.

Given the HL test’s sensitivity to sample size, graphs will be constructed based on sequential groups with equal observed events rather than equal patient numbers (thus, low-risk groups will have more patients than high-risk groups).

For evaluating risk prediction accuracy and comparing the universal and procedure-specific surgical risk calculators, the Brier score will be considered the most appropriate measure of model performance. Results from 2 yr of data used for model development will be compared with those from the 3rd year of data used for validation.

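### The only measure of overfitting is a split-sample comparison that is inconsistently defined and open to leakage, and the bootstrap adds no estimate of optimism

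*Protocol article*

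**What the plan says.** All references are to the protocol article.

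- **Split (section 4.3).** Internal validation is done by "randomly splitting the analytic dataset into two subsets", two-thirds for development and one-third for validation. C-indices, Hosmer-Lemeshow analyses and Brier scores "will be compared between the developmental model applied to the developmental dataset and the same model applied to the validation dataset".
- **Bootstrap (section 4.3).** To test robustness, "bootstrap resampling will be employed for the postoperative mortality model". In it, "Full-variable logistic regression models will be performed on each bootstrap sample". Variables are ranked by Wald chi-square, and "the average rankings from the bootstrap samples will be compared with the order of entry of variables" in the forward stepwise analysis. The section closes by presenting all these steps as aimed at limiting overfitting.
- **Second division of the data (section 4.1).** "Results from 2 yr of data used for model development will be compared with those from the 3rd year of data used for validation".
- **Data span (section 3.7).** The cystectomy cohort covers 2000 to 2021 and the prostatectomy cohort 2000 to 2020. The primary outcomes are the CDC/CAMUS grade or death within 90 days, and the Comprehensive Complication Index.
- **Nomograms and screening.** Section 3.2 builds the nomogram from the CAMUS database, supplemented by the Bern cystectomy database. In section 3.3, under the first Delphi round, "Experts will be guided by the results derived from nomograms". Section 4.1 begins with univariate screening of each pre- and intraoperative variable in the database.

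**The concern.** A model built by screening at p ≤ 0.20, stepwise selection and rounding to points looks better in its own data than in new patients. Internal validation exists to measure that gap. Three features of the plan weaken the measurement.

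1. The bootstrap is counted among the safeguards against overfitting but produces no performance figure. It also leaves out the models for the CDC/CAMUS outcome and the Comprehensive Complication Index.
2. Two divisions of the data into development and validation sets are stated and not reconciled. The reported performance depends on which is used.
3. If screening or expert choice of predictors draws on all the data, the held-out third is no longer independent of the model it tests.

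The result is meant to be a calculator for patient counselling and for comparing surgeons and hospitals (sections 5.1 and 5.1.2). Optimistic validation figures would carry straight into those uses.

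**Working it through.** **1. What each step can estimate.** Optimism is performance in the data used to build the model minus performance in new data.

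- Split: optimism ≈ C(development) − C(validation), and likewise for the Brier score. Section 4.3 plans exactly this comparison. It is valid if every data-driven choice is made in the development part.
- Bootstrap as planned: the full-variable model is refitted in each resample, so screening and selection are not repeated. The output is an average rank per variable. No c-statistic, slope or Brier score is computed, so no optimism can be derived from it.
- The split comparison is described for the logistic regression analyses. The tool itself is a rounded 10- or 20-point score (section 4.1), and no development-versus-validation comparison of that score is stated.

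**2. The two divisions side by side.** Section 4.3 divides at random, 2:1. Section 4.1 divides by calendar time, two years to one, which implies a three-year dataset. The two dated cohorts span about two decades each, and no three-year window is named. The sample-size text in section 3.7 fits the random split: adding 50% means development is 1/1.5 = 2/3 of the total.

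**3. The route by which held-out data could shape the model.** CAMUS and Bern data → nomogram (3.2) → guidance to experts in Delphi round 1 (3.3) → agreed parameters. Section 3.3 says the difficulty score is developed and validated on these same data, with prospectively collected parameters added. Screening (4.1) refers to the database, not to the development subset. Against this, the abstract places the nomogram in the third phase, after the Delphi. The sequence is therefore unclear.

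**4. The plan's sample size, for context.** The stated requirement is 1180 (30 predictors, odds ratio 1.2, 80% power, alpha 0.05, plus 50%). The article does not say how the odds ratio was converted to an effect size, so the figure can be neither confirmed nor called wrong. With f² = (ln 1.2)² = 0.0332 and 30 predictors, N = 761, and 761 × 1.5 ≈ 1142. The point does not rest on this. At 1180 the split gives 787 for development and 393 for validation, and 3% deaths (assumed) would put 393 × 0.03 ≈ 12 deaths in the validation third.

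**5. Illustrative simulation.** Assumed: 30 independent candidates, 6 of them true with odds ratio 1.2 per SD, backward selection at p 0.05, and event rates of 3% and 20%. There were 200 replicates per setting; 164 to 200 were usable after dropping those with too few events or no variable selected. N is the stated minimum (1180) or the Bern cohort (1550). Entries are mean c-statistics. The true value is from 100,000 simulated patients.

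| N, event rate | Development | Validation, selection in development part | True | Validation, selection on all data | True |
|---|---|---|---|---|---|
| 1180, 3% | 0.699 | 0.537 | 0.537 | 0.654 | 0.544 |
| 1180, 20% | 0.638 | 0.574 | 0.578 | 0.614 | 0.592 |
| 1550, 3% | 0.683 | 0.541 | 0.540 | 0.638 | 0.548 |
| 1550, 20% | 0.636 | 0.585 | 0.587 | 0.616 | 0.599 |

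With selection kept in the development part, the validation c is within 0.004 of the truth, so the split works. With variables chosen on all the data, validation exceeds the truth by 0.654 − 0.544 = 0.110, 0.614 − 0.592 = 0.022, 0.638 − 0.548 = 0.090 and 0.616 − 0.599 = 0.017. A single split is also imprecise. With selection in the development part, the SD of the validation c at N = 1180 was 0.084 at 3% events (1.96 × 0.084 ≈ 0.16) and 0.037 at 20% (1.96 × 0.037 ≈ 0.07).

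**The case against.** A reader might infer that the plan has no measure of overfitting at all. The document does not support that. Section 4.3 compares discrimination, calibration and Brier score of the same model in development and validation data, for the prediction models generally and not only for mortality. The simulation shows that this recovers the true performance when it is kept clean.

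A reader might also infer that the held-out data have already shaped the predictors, or that published performance will be optimistic. Neither is established. The article does not say whether the expert nomograms use all the data, the abstract's order would remove that route in round 1, and a fuller analysis plan may confine the screening. Leakage is something the text permits, not something it prescribes.

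Three further points are fair:

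- The bootstrap is introduced as a robustness check on the order of stepwise entry, supplementing the split.
- The two-year/third-year sentence follows the comparison of universal and procedure-specific calculators and could describe a separate temporal check.
- Giving up a third of the data is a matter of efficiency, which section 3.7 openly pays for.

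These soften the point without removing it. A stability check on rankings still does not address overfitting, and a three-year frame still fits neither dated cohort. The planned prospective external validation (section 4.4) is untouched by all this, which lowers the severity. It comes later, however, and its collaborations are still being explored.

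**Conclusion.** The point holds in this form: one usable measure of overfitting is planned, its definition is inconsistent, it is not protected against reuse of the validation data, and the bootstrap does not back it up. The bootstrap's limits and the conflict between sections 4.1 and 4.3 are stated in the text and need no assumption. Leakage is a risk that depends on a sequence the article leaves unclear.

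The size is illustrative only: about 0.02 in the c-statistic at 20% events and 0.09 to 0.11 at 3%. It rests on assumed event rates, effects and independent candidates, and on samples of 1180 and 1550. The first is a stated minimum that section 3.7 places well below what is available. The simulated leak is a complete selection on all the data; screening alone or expert guidance would probably leak less. The matter should be fixed before the models are built, but it does not invalidate the project.

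**What to change.** 1. **One scheme.** Delete the two-year/third-year sentence in section 4.1, or redefine it as a temporal check with dates that the cohorts contain.
2. **A bootstrap that measures optimism.** Replace the Wald-ranking bootstrap with one that repeats screening, selection and point assignment in every resample, for each primary-outcome model and for mortality. Report the optimism-corrected c-statistic, calibration slope and Brier score. Preferably develop the models on all eligible data, which makes the random split unnecessary.
3. **If the random split is kept.** State that screening, selection and any nomogram shown to the Delphi experts use the development part only, and make the order of nomogram and Delphi the same in the abstract and section 3.3.

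The cost is computing time and wording; no additional patients are needed. Shrinkage of the coefficients and leave-one-centre-out validation are reasonable options but are not required to resolve this point.
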